### Data collection

Data will be collected using the search function of EPIC Hyperspace and assistance from HHS and SJHH Information Technology (IT) services teams. The MRN numbers of patients meeting the inclusion criteria will be identified. The data will be exported directly to excel. Any missing data from IT reports will be entered via manual chart review. For each recruited patient, the following baseline characteristics will be recorded to determine factors associated with intolerance of IEN or CEN and with the development of ICU-acquired diarrhea. The baseline characteristics will include demographic data, anthropometric data, clinical data on Day 1 of ICU stay (surgical, medical vs trauma admission, diagnostic category, admitting diagnosis, ventilation status, inotrope/ vasopressor use, renal replacement therapy), admitting hospital, medical comorbidities (prior GI disease, previous luminal surgeries), nutritional assessment (caloric goals on admission will be determined using weight and registered dietician assessment), antibiotic prescription on admission and serum albumin on ICU admission. Table 1 outlines the primary and secondary outcomes as well as the data that will be recorded each day of the ICU admission up until the 30th day or ICU discharge. This includes mode of nutrition (IEN, CEN, oral, or PN), daily caloric intake, mode of ventilation (Invasive, NIPPV), presence of diarrhea, bacteremia greater than 48 hours after admission (gram-positive bacilli and coagulase-negative staph will be reviewed and omitted if team feels it is more likely contaminant), incidence of aspiration pneumonia/pneumonitis, *Clostridioides difficile* infection (CDI), presence of vomiting, ileus or abdominal distention, vasopressor/inotrope dose, average daily insulin dose and blood glucose, survival status in ICU, ICU length of stay. Survival to hospital discharge and hospital length of stay will be collected for the entire hospital stay.

**Table 1 pone.0322122.t001:** Statistical Plan.

Research Objectives	Outcome	Covariates/Subgroups	Analytical Approach
To determine the incidence of diarrhea amongst patients on IEN and CEN	WHO-defined diarrhea	N/A	Descriptive statistics (proportion of patients with diarrhea) and corresponding 95% CI

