To determine risk factors associated with diarrhea during ICU admission	**Dependent Variable** WHO-defined diarrhea	Age, sex, type of nutrition (IEN/CEN), antibiotics, GI comorbidities, vasopressor/inotropes, daily caloric intake, NIPPV, surgical/trauma/medical admission	Logistic Regression
Secondary Outcomes			
**Research Objectives**	**Outcome**	**Covariates/Subgroups**	**Analytical Approach**
To determine whether IEN or CEN is better for reaching caloric requirements during ICU stay	**Dependent Variables:** Average caloric intake (percent goal determined by RD or 25 kcal/kg) at 48 hours and 7 days after initiation of CEN/IEN Proportion of patients on PN at 48 hours and 7 days after initiation of CEN/IEN	NIPPV, Age, sex, antibiotics, GI comorbidities, type of nutrition (IEN/CEN) vasopressor/inotropes, daily caloric intake, surgical/trauma/medical admission	Descriptive statistics (average caloric intake) and corresponding 95% CI Descriptive statistics (proportion of patients on PN) and corresponding 95% CI Logistic regression
To determine whether IEN or CEN is associated with ICU-acquired bloodstream infection or *Clostridium difficile* infection	Incidence of positive blood cultures drawn at least 48 hours after admission, excluding coagulase-negative staphylococcus unless suspected by ICU team to not be contaminant.	NA	The incidence of bloodstream infections will be computed as the number of new cases during ICU stay divided by the person-time at risk. Descriptive statistics (proportion of patients with ICU-acquired bloodstream infection or *C. difficile infection*) and corresponding 95% CI
To determine whether IEN or CEN is associated with differences in mortality or length of stay (ICU or hospital)	**Dependent Variables** Mortality (ICU and hospital) Length of stay (ICU and hospital)	Age, sex, type of nutrition (IEN/CEN), antibiotics, GI comorbidities, vasopressor/inotropes, daily caloric intake, NIPPV, surgical/trauma/medical admission	Descriptive statistics (mortality and length of stay) and corresponding 95% CI Logistic regression

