### Outcomes

The primary outcome is the incidence of diarrhea defined according to the WHO definition (greater than 3 liquid bowel movements in 24 hours) any time during the index ICU admission (Table 1). This will be identified from nursing flowsheets in EPIC. The secondary outcomes include mortality (ICU and hospital), length of stay (ICU and hospital), incidence of confirmed or suspected hospital-acquired blood stream infections or central line associated blood stream infections, incidence of aspiration pneumonia/pneumonitis (identified pragmatically as documented by the ICU team), CDI, percentage of caloric requirements received by enteral nutrition (daily caloric requirements defined as 25 kcal/kg/day1 and by registered dietician assessment), incidence of vomiting, ileus and abdominal distention, and glycemic control (using average daily insulin dose and average daily glucose as a surrogate) (Table 1).

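### Table 1 identifies ICU-acquired bloodstream infection by culture timing and a contaminant exclusion only, so a bacteremia carried over from admission can be counted

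*Protocol article*

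**What the plan says.** The bloodstream infection row of Table 1 in the protocol article has three relevant parts.

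- Objective: "To determine whether IEN or CEN is associated with ICU-acquired bloodstream infection" (or *C. difficile* infection).
- Outcome: "Incidence of positive blood cultures drawn at least 48 hours after admission", with one exclusion: "excluding coagulase-negative staphylococcus unless suspected by ICU team to not be contaminant".
- Analysis: a rate, the "number of new cases during ICU stay divided by the person-time at risk", and a proportion of patients with ICU-acquired infection, with a 95% CI. The covariate cell is NA.

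The text under Data collection lists, as a daily item, "bacteremia greater than 48 hours after admission", with a somewhat wider contaminant review: "gram-positive bacilli and coagulase-negative staph will be reviewed and omitted if team feels it is more likely contaminant". The Outcomes section words the outcome differently: "incidence of confirmed or suspected hospital-acquired blood stream infections or central line associated blood stream infections".

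Baseline items under Data collection include antibiotics and albumin on admission, but no blood culture result. The exclusion criteria under Participants do not mention infection or bacteremia on admission. The Feasibility section says that microbiology is readily accessible and can be sorted without manual chart review.

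**The concern.** The objective is infection acquired in the ICU. The rule that picks out cases looks at when the culture was drawn and whether the organism is a likely contaminant. It does not look at whether the patient was already bacteremic. Take a patient who is positive on arrival and still positive with the same organism at hour 60. That patient meets the written outcome definition, although the infection began before any ICU feeding and so cannot be an effect of feeding mode.

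At stake is one secondary outcome. Carry-over cases add events unrelated to IEN or CEN, and the row plans no covariate adjustment that might absorb an imbalance between the groups.

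**Working it through.** **Plan's own figure.** The only sample-size figure, 455 per group, belongs to diarrhea and has no bearing here. The documents give no rate of bloodstream infection, admission bacteremia or persistent positivity.

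**Step 1: does any stated rule remove carry-over?**

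| Place in the protocol article | What it does | Removes a persisting admission bacteremia? |
|---|---|---|
| Table 1, outcome | 48-hour timing; contaminant exclusion | No |
| Data collection, daily items | 48-hour timing; contaminant review | No |
| Data collection, baseline items | No admission culture listed | No |
| Participants, exclusions | Bacteremia on admission not listed | No |
| Table 1, objective and rate | The words ICU-acquired and new cases | Intended, but no rule for judging it |
| Pilot testing; Data adjudication | 40 and 50 charts, checking the IT reports | No rule stated |
| Feasibility | Microbiology sorted without manual review | No |

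The intent is clear, but the steps that identify cases do not carry it out.

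**Step 2: how much could it matter?** All inputs are assumptions.

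- p = true ICU-acquired incidence, 5% in both groups
- b = share bacteremic on admission, 5% to 15%
- r = share of these with a positive culture at 48 hours or later, 10% to 30%

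If carry-over is independent of true infection, the counted proportion is p + (1 − p) × b × r, and the carry-over share of counted cases is (counted − p) / counted.

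| b | r | Counted proportion | Carry-over share |
|---|---|---|---|
| 5% | 10% | 0.05 + 0.95 × 0.005 = 0.0548 | 8.7% |
| 5% | 30% | 0.05 + 0.95 × 0.015 = 0.0643 | 22.2% |
| 10% | 20% | 0.05 + 0.95 × 0.020 = 0.0690 | 27.5% |
| 15% | 30% | 0.05 + 0.95 × 0.045 = 0.0928 | 46.1% |

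**Step 3: effect on the comparison.**

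- No true effect, equal b (5% and 5%): the odds ratio stays 1.00 for every r.
- No true effect, b = 5% (IEN) and 10% (CEN): odds ratio 0.92 at r = 10%, 0.81 at r = 30%.
- No true effect, b = 10% (IEN) and 15% (CEN): odds ratio 0.92 at r = 10%, 0.83 at r = 30%.
- A true difference, equal b: suppose true incidences of 4% and 7%, a ratio of 0.07 / 0.04 = 1.75. With b = 10% and r = 20%, the counted values are 0.04 + 0.96 × 0.02 = 0.0592 and 0.07 + 0.93 × 0.02 = 0.0886, a ratio of 1.50. The absolute difference barely moves (0.0300 to 0.0294).

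Which group was given the higher b is arbitrary, so the direction of the spurious odds ratios has no meaning.

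**The case against.** The best defence is that the row must be read as a whole. It names ICU-acquired infection and counts new cases, and the Outcomes section says hospital-acquired. On an ordinary reading, a bacteremia present on arrival is not new. The article is also condensed: a look-back window could sit in a fuller plan or be settled in the pilot, where two reviewers adjudicate each chart on the secondary outcomes.

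Much of this stands, and it rules out several stronger readings that a reader might infer:

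- That every positive culture after 48 hours counts. It does not: likely contaminants are excluded.
- That carry-over will certainly be scored as a complication of feeding. The words new and ICU-acquired point the other way, so the most that can be said is that it can be counted.
- That several positive cultures from one episode inflate the proportion. A patient counts once there. Only the person-time rate could be affected, and only if new is not applied.
- That the IEN-CEN comparison is biased. Nothing in the documents shows that admission bacteremia differs by feeding mode.

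The defence does not dispose of the point. The article does not leave the case definition open: it states one, with its exclusions, and that definition is wider than the objective. A clear positive at hour 60 is neither missing nor unclear, so it would not trigger the manual review that the pilot section keeps. The listed data items would not let an analyst tell new from persisting.

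**Conclusion.** The concern holds in a limited form. The stated definition of bloodstream infection does not put ICU-acquired or new into operation, so a bacteremia carried over from admission can enter the count. Equal carry-over would inflate both groups' rates and pull a true ratio towards 1. Bias in the comparison needs a further condition: a difference between the groups in admission bacteremia or in its persistence.

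The size cannot be derived from the documents. The range of about 9% to 46% of counted cases rests wholly on the assumed inputs and on nobody applying the word new during extraction; its top end takes b and r both at their highest. The primary outcome is untouched. The point is worth correcting because a stated rule can give wrong counts and the remedy is simple.

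**What to change.** 1. In Table 1, define a case as a qualifying positive culture at or after the 48-hour mark whose organism was not isolated from any blood culture drawn before that mark. Keep the contaminant exclusion.
2. Add blood culture results from before the 48-hour mark to the extracted data, since the look-back cannot be applied without them.
3. In the person-time rate, count repeat positives of the same organism in a patient as one case.
4. Use this same case definition for the rate and for the per-patient proportion, and align the wording under Data collection and Outcomes with it.

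The cost is a wider date range and one filter on a microbiology export that the article already calls readily accessible. There is a small downside: a true re-infection with the same organism would be missed, and the reported rate may be somewhat lower.

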While guidelines agree on the value of early EN, there is little consensus on how feeds should be delivered [1,4]. Broadly, there are two methods for EN delivery: continuous enteral feeding (CEN), which consists of low rates of tube feeds over a 24-hour period, and bolus/intermittent enteral feeding (IEN), which consists of higher rates of tube feeds delivered over shorter time periods. The American Society of Parenteral and Enteral Nutrition (ASPEN) recommends avoidance of IEN in high-risk patients based on 2 small RCTs which showed a trend towards higher mortality with IEN (13.9% IEN vs 7.4% CEN; p = 0.18) and increased risk of ventilator association pneumonia with IEN (49.3% IEN vs 30.9% CEN, p=0.02) [1,7,8]. However, both trials were published more than 15 years ago. The European Society of Parenteral and Enteral Nutrition (ESPEN) recommends avoidance of IEN in general, citing trends towards worsening diarrhea in 5 small prospective studies [4]. In contrast, 2 meta-analyses, one including 5 RCTs (392 patients) and the other including 9 RCTs (690 patients) have shown no important difference in diarrhea, vomiting, nausea or mortality in patients fed via IEN vs CEN [9,10].

Just as the mode of EN delivery is understudied, so too are the effects of critical illness on the GI tract. Feeding intolerance, diarrhea, vomiting, and ileus are common and associated with increased mortality [11]. While challenging to define, a recent multi-center cohort study found the incidence of diarrhea was as high as 38% with various definitions [12]. Diarrhea has been consistently shown to increase length of stay and contribute to morbidity in ICU patients [11–12,14]. While EN in general has been associated with higher rates of diarrhea [13], the effect of EN strategy (IEN vs CEN) on diarrhea is still unclear. Two recent RCTs including 120 and 112 mechanically ventilated patients respectively found no significant difference in diarrhea, constipation or vomiting [15,16].

Taken together, EN has become the standard of care for most critically ill patients, but little is known about optimal EN strategy or its effect on diarrhea. This is a pragmatic retrospective cohort study that will compare patients receiving IEN and CEN by determining the differences in diarrhea incidence and nutritional exposures, such as the type and volume of EN that patients receive.

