### Participants

We will include all patients 18 years of age or older admitted to the ICU for at least 24 hours who have a prescription for EN or are receiving NIPPV for greater than 48 hours. Patients who received majority NIPPV for 48 hours at any one time will also be included even if they were not prescribed EN. EPIC Hyperspace is now the Electronic Medical Record (EMR) used in hospitals in Hamilton. We will include patients admitted to the ICU since EPIC went live at each site. For St. Joseph’s Hospital Hamilton (SJHH) this is between January 1, 2018, and December 31, 2023. For the two sites at Hamilton Health Sciences (HHS), this is between June 4, 2022, and December 31, 2023. Exclusion criteria includes patients receiving only nocturnal NIPPV, patients who have had gastrointestinal surgery in the month preceding ICU admission, and patients who have confirmed or suspected luminal obstruction on admission. For the purposes of this study NIPPV will exclude high flow nasal canula (HFNC).

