For the secondary outcomes patients also be divided into those who have received NIPPV and those who have not. For the purposes of this study, NIPPV will exclude HFNC but will include bilevel positive airway pressure (BiPAP) and continuous positive airway pressure (CPAP) delivered via any interface. To evaluate the relationship between IEN, CEN and NIPPV on caloric goals, each patient’s caloric intake at 48 hours and 7 days will be divided by their 24 hour caloric target (as determined by RD assessment and by the algorithm 25 kcal/kg) (Table 1). The average of these percentages with associated 95% CI will be calculated in each group. The proportion of patients in each group receiving supplement parenteral nutrition at these time points will also be determined to help evaluate the effectiveness of each EN strategy (Table 1). Logistic regression will also be applied to evaluate the role of covariates; specifically baseline characteristics and the effect they may have on patients reaching their caloric targets (Table 1). In terms of other secondary outcomes, the incidence of hospital acquired infections, ICU and hospital mortality will be determined per person-time at risk in each group (IEN vs CEN) with associated 95% CI. Significant differences between groups will again be determined by two sample t-test. Multivariate logistic regression will evaluate associations between baseline characteristics and the type of EN chosen.

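### Length of stay is compared between feeding groups without separating stays that end in death from stays that end in live discharge

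*Protocol article*

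**What the plan says.** The relevant row of Table 1 states a between-group objective: "To determine whether IEN or CEN is associated with differences in mortality or length of stay (ICU or hospital". ICU and hospital length of stay are dependent variables in that row, next to mortality. The analytical approach is "Descriptive statistics (mortality and length of stay) and corresponding 95% CI", followed by logistic regression. The covariates are age, sex, feeding type, antibiotics, GI comorbidity, vasopressors or inotropes, caloric intake, NIPPV and admission type.

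The Outcomes section lists stay as an outcome in its own right: "The secondary outcomes include mortality (ICU and hospital), length of stay (ICU and hospital". The Participants section sets no survivor restriction: "We will include all patients 18 years of age or older admitted to the ICU for at least 24 hours", subject to the feeding or NIPPV criterion and the exclusions.

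For mortality, the Data analysis section uses a time-based denominator: "ICU and hospital mortality will be determined per person-time at risk in each group (IEN vs CEN) with associated 95% CI". It does not extend this, or any other handling of death, to length of stay.

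The Data collection section shows that the needed data exist. Survival status in ICU and ICU length of stay are among the recorded items, and "Survival to hospital discharge and hospital length of stay will be collected for the entire hospital stay".

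**The concern.** Death ends a stay and rules out discharge alive. In a summary of stay over all patients, a death on day 3 and a recovery with discharge on day 3 contribute the same value. The summary therefore mixes time to recovery with time to death, in proportions set by each group's mortality.

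If both groups have the same mortality, with deaths at similar times, this mixing largely cancels in the comparison. If they do not, a difference in mortality appears as a difference in stay. A group with more early deaths can then look as though its patients recover sooner. The stated objective is about the association of feeding mode with stay, and a reader would naturally take a shorter stay as favourable. The Strengths and limitations section expects the results to inform post hoc analyses of an upcoming randomised trial of the same comparison, so a misread difference could carry forward.

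**Working it through.** **Figures in the plan.** The article gives no expected length of stay, no mortality for this cohort and no precision target for this outcome. Its only design figure, 455 per group, concerns diarrhea. It reproduces from 25.1% versus 17.5% (two-sided alpha 0.05, power 0.8, pooled variance) but has no bearing here.

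**Inputs for the illustration**
- Mortality 13.9% and 7.4%: cited in the Introduction from outside this cohort, used only as an example of unequal mortality.
- Mean survivor stay *S* = 12 days in both groups: assumed.
- Mean decedent stay *D* = 4 to 16 days, the same in both groups: assumed.

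**Step 1: all-patient mean.** With mortality *m*, mean stay = *m*·*D* + (1 - *m*)·*S*. With *S* and *D* common to both groups, the difference is (*m*₁ - *m*₂)·(*D* - *S*) = 0.065·(*D* - 12).

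| Decedent stay *D* (days) | Mean at 13.9% mortality | Mean at 7.4% mortality | Difference (days) |
|---|---|---|---|
| 4 | 10.89 | 11.41 | -0.52 |
| 6 | 11.17 | 11.56 | -0.39 |
| 8 | 11.44 | 11.70 | -0.26 |
| 12 | 12.00 | 12.00 | 0 |
| 16 | 12.56 | 12.30 | +0.26 |

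Survivors' stays are identical throughout, so every non-zero difference comes from mortality alone. The sign depends on whether those who die stay for less or more time than survivors.

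**Step 2: longer stays.** For hospital stay with assumed *S* = 25 to 30 and *D* = 10 to 12 days, the same formula gives 0.065·(12 - 25) = -0.8 to 0.065·(10 - 30) = -1.3 days.

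**Step 3: timing alone.** Mortality need not differ. With 20% mortality in both groups (assumed) and the same *D*, the difference is 0. If decedents stay 4 days in one group and 8 in the other, it is 0.20·(4 - 8) = -0.8 days.

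**Step 4: same daily chance of discharge.** Suppose instead that both groups have a constant discharge hazard of 1/12 per day (assumed) and a constant death hazard giving 13.9% and 7.4% mortality. Mean stay is 1/(death hazard + discharge hazard) = 12·(1 - *m*), that is 10.33 versus 11.11 days, a difference of -0.78. In this model survivors and decedents within a group have the same mean stay, so a split by vital status would still show 10.33 versus 11.11 among survivors. The cumulative incidence of discharge alive by day *t*, (1 - *m*)·(1 - exp(-*t*/mean)), behaves correctly. At day 12 it is 0.861·(1 - exp(-12/10.33)) = 59.1% versus 0.926·(1 - exp(-12/11.11)) = 61.2%, and it ends at 86.1% versus 92.6%. The higher-mortality group no longer looks better.

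**The case against.** **This is an omission in a condensed article.** No sentence says that stay is summarised over all patients. That is inferred from broad eligibility and the absence of any restriction, and a fuller plan could contain a rule. This lowers the weight but does not remove the point. Table 1 is presented as the statistical plan, sets the comparison and names the method for it, and that method does not answer the stated objective when mortality differs.

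**A reader might infer that mortality is unequal here and that IEN stay will look spuriously short.** The documents do not support this. The Introduction reports a "trend towards higher mortality with IEN (13.9% IEN vs 7.4% CEN; p = 0.18". It attributes the evidence to small trials, notes their age, and sets against them two meta-analyses (392 and 690 patients) with no important mortality difference. Decedents' stays are not given anywhere. The IEN group rule in Data analysis, which requires two complete days of IEN, would also tend to keep very early deaths out of the IEN group, which could push the other way.

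**A reader might also attach an inflated false-positive rate to the plan.** That needs a specific test of mean stay. The sentence "Significant differences between groups will again be determined by two sample t-test" follows infections and mortality and does not name length of stay, so no error rate can be stated as a property of this plan.

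**Mortality is reported in the same row, and all-patient stay is a legitimate measure of resource use.** Both are true. Seeing mortality alongside alerts the reader but does not correct the estimate, and resource use is not what the objective is likely to be read as asking.

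**A simple split by survival status would be enough.** It helps as description, but step 4 shows that it need not remove the artefact.

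**Conclusion.** The point holds as a matter of interpretation for a secondary outcome. Followed as written, the length-of-stay comparison mixes recovery with death, and any difference between the groups in how often or when patients die will enter it.

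Its direction and size in this cohort are unknown. If the stay of survivors and the stay of decedents are each the same in both groups, the higher-mortality group appears to have a shorter stay when decedents stay less time than survivors, shows no shift when they stay equally long, and appears to have a longer stay when they stay longer. The illustrations run from -1.3 to +0.26 days. They rest on mortality borrowed from outside the cohort, or an assumed 20% in step 3, and on assumed stays. They show the mechanism and are not a forecast. The change is worth making before analysis because it is cheap; it does not touch the primary outcome.

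**What to change.** In Table 1 and in Data analysis:

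1. Define the length-of-stay analyses as time to discharge alive from ICU and from hospital, with death as a competing event, and report the cumulative incidence of discharge alive by feeding group with 95% CI.
2. Report stay separately for survivors and for those who died, as description.
3. If an all-patient stay is also shown, label it as resource use and state that it is not interpreted as a feeding effect.

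No new data are needed, since survival status and length of stay are already collected for both ICU and hospital. If ICU records stop at the 30-day limit of daily collection, patients still in ICU should be treated as censored then. The cost is a change of wording and a cumulative incidence or split summary in place of one mean or median.

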To determine whether IEN or CEN is associated with differences in aspiration pneumonia/pneumonitis	Incidence of aspiration pneumonia/pneumonitis, determined pragmatically by ICU team	NA	The incidence of aspiration pneumonia/ pneumonitis will be computed as the number of new cases during ICU stay divided by the person-time at risk. Descriptive statistics (proportion of patients with aspiration pneumonitis/ pneumonia) and corresponding 95% CI

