## Discussion

EN has become the standard of care for nutritional support in most critically ill patients. Despite this, nutrition and the consequences of delivering it are discussed by multidisciplinary teams and often family members daily in the ICU. Abdominal pain, distention, vomiting, and diarrhea are frequent [11], and there is little to no high-quality evidence outlining which EN strategies best mitigate these risks. Institutional practices and practitioners’ comfort with specific strategies often dictate the EN method.

Diarrhea is a frequent problem amongst critically ill patients that is also understudied. It has been shown in a recent multicentre prospective study to affect greater than 38% of critically ill patients [12]. Moreover, diarrhea is particularly distressing to patients and their families and has been shown in several studies to be associated with increased length of stay. Selecting an EN strategy that would be less likely to result in diarrhea would be valuable to clinicians and patients alike.

Physiological studies have suggested the potential benefits of IEN over CEN [20]. This is despite CEN being more common than IEN in most critical care units [20]. In healthy volunteers, IEN causes more rapid gastric emptying, increased superior mesenteric arterial flow, and physiologic insulin peaks compared to CEN [20]. While caution should be used when generalizing these findings to critically ill patients, a small RCT of 120 patients did find that mechanically ventilated patients on IEN were more likely to meet caloric targets. Furthermore, interrupted feeds for procedures and loss of enteral access are more likely to affect the daily caloric intake amongst patients on CEN. With malnutrition still being a large problem in Canadian ICU, IEN may be a potential solution and led us to evaluate the effects of EN strategy on the daily caloric intake and PN [21]

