### Strengths and limitations

This is a pragmatic study with broad inclusion criteria that should be generalizable to most critically ill patients. It uses the newly implemented EMR at all institutions in Hamilton to generate a large amount of patient data without manual review. It examines two understudied areas of critical care medicine, the effects of EN strategy on diarrhea and the effect of NIPPV on nutrition.

The main weakness in our study is the retrospective strategy. It may be challenging to understand whether differences in diarrhea and daily caloric intake are due to covariates and the severity of illness or the EN strategy chosen. Furthermore, our study centres are all located in Hamilton, Canada; meaning that our findings may be less generalizable to other centres with different practice patterns.

The ENND-GOALs study will generate relevant, pragmatic data regarding EN strategy and diarrhea in the critically ill. Moreover, it will support the findings and inform posthoc analysis from the upcoming INVENTS-ICU RCT, which will also evaluate the differences between IEN and CEN.

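### Two Table 1 rows (bloodstream infection/C. difficile, and aspiration) ask whether feeding mode is associated with the outcome but plan only crude summaries, although feeding mode is not randomised and the mortality row is adjusted

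*Protocol article*

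**What the plan says.** In Table 1 (Data collection section), the last row has the objective "To determine whether IEN or CEN is associated with differences in aspiration pneumonia/pneumonitis". Its covariate cell reads NA. The planned analysis is new cases over person-time at risk, plus the proportion of patients affected with a 95% CI. The bloodstream infection/C. difficile row also asks whether IEN or CEN is associated with the outcome, also has NA for covariates, and plans the same kind of crude summary.

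The mortality row is worded alike, "To determine whether IEN or CEN is associated with differences in mortality or length of stay (ICU or hospital", but lists nine covariates, among them "vasopressor/inotropes, daily caloric intake, NIPPV, surgical/trauma/medical admission", and adds logistic regression to the descriptive statistics.

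The Data analysis section says "For the secondary outcomes patients also be divided into those who have received NIPPV and those who have not". It spells this out only for calories ("To evaluate the relationship between IEN, CEN and NIPPV on caloric goals"). It then says that "the incidence of hospital acquired infections, ICU and hospital mortality will be determined per person-time at risk in each group (IEN vs CEN") with 95% CIs, and that group differences will be tested by a two-sample t-test. The last regression in that section models which type of EN was chosen, not any infection or aspiration outcome.

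**The concern.** This is a retrospective cohort. The Discussion says that institutional practice and practitioners' "comfort with specific strategies often dictate the EN method", and the Introduction reports guideline advice against IEN in high-risk patients. Feeding mode may therefore track hospital and patient risk. Under Strengths and limitations, the protocol concedes that it may be hard to tell whether differences are "due to covariates and the severity of illness or the EN strategy chosen", but it says so only for diarrhea and caloric intake.

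For infection and aspiration the plan asks a comparative question and supplies no estimate that could separate mode from case mix. The Introduction cites a difference in ventilator-associated pneumonia by feeding mode (49.3% IEN vs 30.9% CEN). That is a different outcome, but it makes it plausible that a crude aspiration contrast would be read as safety evidence.

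**Working it through.** **1. The plan's own figure.** The protocol gives no sample size or expected rate for infection or aspiration. Its only calculation concerns diarrhea: 25.1% vs 17.5%, two-sided alpha 0.05, power 0.80. With pooled variance, n = [1.96·√(2·0.213·0.787) + 0.842·√(0.251·0.749 + 0.175·0.825)]² / 0.076² = 454.4, so 455 per group, as stated. Nothing below depends on it.

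**2. The rows side by side.**

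| Table 1 row | Asks about IEN vs CEN | Covariates | Regression |
|---|---|---|---|
| Mortality, length of stay | yes | nine listed | logistic |
| Bloodstream infection, C. difficile | yes | NA | none |
| Aspiration | yes | NA | none |

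No other section supplies an adjusted IEN versus CEN estimate for the last two rows.

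**3. How far confounding could move a crude ratio (all inputs assumed).** Suppose feeding mode has no effect and a baseline factor, for example NIPPV, multiplies risk by k. Let it be present in a share s1 of IEN and s0 of CEN patients. Then

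crude IEN/CEN ratio = (1 + s1(k − 1)) / (1 + s0(k − 1)).

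| k | s1 = 0.2, s0 = 0.4 | s1 = 0.4, s0 = 0.2 | equal shares |
|---|---|---|---|
| 0.5 | 1.13 | 0.89 | 1.00 |
| 1 | 1.00 | 1.00 | 1.00 |
| 1.5 | 0.92 | 1.09 | 1.00 |
| 2 | 0.86 | 1.17 | 1.00 |
| 3 | 0.78 | 1.29 | 1.00 |

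The protocol gives none of k, s1 or s0, so neither the direction nor the size can be fixed.

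**4. Precision, and the cost of adjusting for ventilation.** The Sample size section expects about 500 patients and fewer on IEN. Assumed: 150 IEN and 350 CEN, or 120 and 280 if only 400 receive EN; events in 5%, 10% or 15%; equal person-time; equal risk across strata; invasive/NIPPV/neither shares of 60/20/20% in IEN and 40/40/20% in CEN. With d1 and d0 the event counts in IEN and CEN, and d1s and d0s those within stratum s:

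- crude SE of the log rate ratio = √(1/d1 + 1/d0)
- adjusted SE = 1/√Σ[d1s·d0s/(d1s + d0s)]

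Example, 150/350 at 10%: d1 = 15, d0 = 35, crude SE = 0.309, CI factor exp(1.96 × 0.309) = 1.83. Stratum events are 9, 3, 3 in IEN and 14, 14, 7 in CEN. The sum is 5.48 + 2.47 + 2.10 = 10.05, so adjusted SE = 0.315 and the factor is 1.86.

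| Split | Events | Crude CI factor | Adjusted CI factor |
|---|---|---|---|
| 150/350 | 25 / 50 / 75 | 2.35 / 1.83 / 1.64 | 2.40 / 1.86 / 1.66 |
| 120/280 | 20 / 40 / 60 | 2.60 / 1.97 / 1.74 | 2.66 / 2.00 / 1.76 |

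The SE ratio is about 1.02 throughout (1.025 with the shares reversed). This covers ventilation status only. Adding admitting hospital costs more if the hospitals differ sharply in their use of IEN, and the documents do not show whether they do.

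**5. Comparison.** The largest assumed bias is a factor of 1.29 (or 1/0.778 = 1.29). The narrowest CI factor is 1.64. The assumed bias is below sampling error in every scenario.

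**The case against.** The strongest reply is that Table 1 is consistent: it models diarrhea, calories and mortality/length of stay, and describes infection and aspiration. Few events would be a sensible reason. At an assumed 5% rate there are 20 to 25 aspiration events, or 2.2 to 2.8 for each of the nine covariates in the mortality row. The word associated can also be read descriptively, and the NIPPV split is announced for the secondary outcomes without restriction. This stands in part. It rules out copying the nine-covariate model, and it means that the aspiration row is not an isolated slip. But the protocol gives no such reason, the objectives are worded like the mortality one, and a NIPPV split or t-test yields no adjusted IEN versus CEN estimate.

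A second reply is that assumed bias below sampling error makes this minor. That limits the weight of the point. It does not remove it, because a confidence interval shows sampling error and not confounding.

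A reader might go further and infer from the Discussion's aspiration figures (17% vs 4%) that the crude contrast will be badly biased, or biased in a known direction. The documents do not support this. Those figures compare EN with no EN among patients on NIPPV and say nothing about IEN versus CEN. Nor is ventilation mode shown to be the confounder that matters most; the protocol's own account points at least as much to institutional practice and severity.

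**Conclusion.** The point holds for both rows. The objectives are comparative, the covariate cells are fixed as NA, and the planned analysis cannot separate feeding mode from the patients who received it. This is a stated choice in a table titled as the statistical plan, not a detail left to another document. The size and direction of confounding are unknown. The range of 0.78 to 1.29 rests wholly on assumed NIPPV shares and risk multipliers, and lies within the sampling error under the assumed event rates and group sizes. Only secondary outcomes are affected; diarrhea has its own regression that includes feeding mode. The case for change is that the mismatch is plain and the remedy cheap, not that a large bias is expected.

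**What to change.** In both rows, keep the crude rates and proportions and replace NA with a short prespecified list: Day 1 ventilation status and admitting hospital, plus vasopressor/inotrope use and admission type if events allow. Among patients classified as IEN or CEN, add a rate ratio from a Poisson model with log person-time as offset.

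For this ratio, start events and person-time once the two-day IEN criterion can be met, for example 48 hours after EN start. Counting from EN start would credit IEN with time during which a patient could not yet qualify. Classification by most study days still uses later data, and this should be stated as a limitation.

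Leave the NIPPV split in Data analysis as it is. Redefining it by the day EN starts would leave the deliberately included NIPPV patients without EN unclassified.

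If events are too few to fit the model, call both objectives descriptive and draw no IEN versus CEN conclusion.

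Cost: two table cells, a short paragraph and one small model per outcome. No new variables are needed: the Data collection section already lists all four covariates at baseline and feeding mode daily. The downsides are a slightly larger standard error (about 2% for ventilation status alone under the assumed inputs), fewer events because early ones fall before the start point, a time window that differs from that of the crude rates and must be labelled, and residual confounding.
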